### ENDIA in the context of international studies investigating the environment and T1D risk

To our knowledge there are no other studies in the Southern Hemisphere or South-East Asia investigating environmental determinants of T1D from pregnancy through early life. Internationally, the ENDIA Study will differ from The Environmental Determinants of Diabetes in the Young (TEDDY) [92], the TRIGR [93] and German BabyDiab [94] studies in that:

• ENDIA includes children on the basis of family history, irrespective of HLA genotype. This is relevant as the rising incidence of T1D is accounted for by individuals with lower risk HLA genotypes.

• Prospective samples will be collected for analysis of the microbiome from the gut (represented by stool), oral cavity, nares, skin and vagina during pregnancy and from breast milk during lactation (including colostrum) and 3-monthly in early childhood. Pregnancy and the first two years of life are critical periods for the development and establishment of the microbiota, underscoring the importance of prospective studies from pregnancy.

• Nutritional status and intake will be documented prospectively during pregnancy (from the first trimester) and lactation [95].

• Weight gain and physical activity (using validated tools [96]) will be measured prospectively during pregnancy.

• Nutritional status and intake in childhood will be documented by daily diary until weaning and then by multi-pass 24-h food recalls [97,98] until 24 months, and from two years by the Australian Toddler Eating Survey [99].

• Fasting blood samples will be collected in childhood to measure insulin resistance.

• The Australian population differs in many ways from those in the USA and Europe, e.g. in diet, UV exposure, and immunisation status (Australia has a much higher RV vaccine uptake than in USA).

### Hypothesis and objectives

#### Hypotheses

The unifying hypothesis is that gene-environment interactions during prenatal and postnatal development drive the development of islet autoimmunity and T1D in children at-risk for T1D.

The specific hypotheses are:

1. The maternal microbiome during pregnancy and lactation differs in composition, diversity and functional products between mothers whose offspring do and do not develop islet autoimmunity and T1D.

2. The microbiome differs in composition, diversity and functional products in children who do and do not develop islet autoimmunity and T1D during the first three years of life.

3. Accelerated weight gain during pregnancy, and accelerated weight gain and insulin resistance during the first three years of life, is associated with an increased risk of islet autoimmunity.

4. Viral infection during pregnancy and first three years of life modifies the risk of islet autoimmunity and T1D.

#### Objectives

1. To follow 1,400 children who have a first-degree relative (FDR) with T1D during pregnancy and early life to determine HLA genotype together with multiple susceptibility genes, changes in the microbiome, weight gain, metabolome-lipidome, insulin sensitivity, nutritional status, inflammatory markers, the timing and frequency of viral infections, and the relationships between genetic and environmental determinants.

2. To determine the relationship between changes in the microbiome and prenatal and postnatal exposures, including weight gain, metabolome-lipidome, insulin sensitivity, nutritional status, and viral infection, and the development of persistent islet autoimmunity in children with a FDR with T1D.

The long-term objective is to follow T1D at-risk children into adolescence to determine the relationship between genotype, the microbiome and the environment, and the development of islet autoimmunity and T1D.

## Methods/design

### Summary of design

This is a prospective cohort study of the offspring of 1,400 mothers who have T1D, or a FDR with T1D, from pregnancy through childhood. Recruitment and consent will occur during pregnancy. The first investigation occurs as soon as feasible after the mother has given consent and investigation is 3-monthly throughout the pregnancy. At birth there is investigation of the mother and child and the child is then followed 3-monthly for two years, and 6-monthly thereafter. The primary outcome measure is persistent islet autoimmunity. The secondary outcome measure is the development of T1D. An overview of the study activities across time is shown in Table 1.

**Table 1 T1:** Study design overview

**Sample (parameter)**	**Description**	**Purpose**	**1**^**st **^**trimester †**	**2**^**nd **^**trimester**	**3**^**rd **^**trimester**	**1-2 days postnatal**	**3-5 days postnatal**	**3 m**	**6 m**	**9, 15, 21, 30 m**	**12, 18, 24, 36 m**	**Proband**
Informed consent	-	Informed consent	*									*
Demographics (including ancestry, socioeconomic status)	-	Maternal	*ψ									
		Paternal	*ψ									
		Infant				*ψ						
		Proband										*
Medical/obstetric history	-	Maternal	*	*	*							
		Paternal	*ψ									
		Proband										*
		OGTT results			*							
		Pregnancy complications					*ψ					
		Labour and delivery					*ψ					
		Congenital abnormalities					*ψ					
Anthropometry	-	Height, Weight, BMI	*	*	*		*					
		Weight z, length z, BMI z				*		*	*	*	*	
		Waist circumference				*		*	*	*	*	
		Lifestyle questionnaire	*	*	*			*	*	*	*	
Blood	A: Serum (red)	AutoAbs: Melbourne			*	*^Δ^		*	*	*	*	
		AutoAbs: Adelaide			*	*^Δ^		*	*	*	*	
		Resistance: adiponectin, hsCRP, C-peptide, insulin, glucose	*	*	*	*^Δ^		*	*	*	*	
		Metabolome/lipidome	*	*	*	*^Δ^		*	*	*	*	
	B: Serum (red)	Vitamin D (25 OHD) / tTGAb / C-peptide / glucose	25 OHD tTGAb	25 OHD tTGAb	25 OHD tTGAb	25 OHD tTGAb C-peptideΔ		25 OHD tTGAb	tTGAb	25 OHD tTGAb	tTGAb glucose (12, 24, 36 m)	
	C: LH (green)	Cytokines/chemokines (innate immunity)						*	*	*	*	
	D: K-EDTA (purple)	Buffy coat (epigenome)	*	*	*	*^Δ^		*	*	*	*	
		RBC	*	*	*	*^Δ^		*	*	*	*	
		Virology	*	*	*	*^ΔΩ^		*	*	*	*	
		DHA, EPA, resolvins, protectins, prostaglandin E2	*	*	*	*^Δ^		*		*		
		Advanced glycation end products	*	*	*	*^Δ^			*		*	
		Haemoglobin A1C (HbA1c)	***††**	***††**	***††**	*^Δ^				*ϕ	*ϕ	
	E: K-EDTA (purple)	HLA typing				*^Δ^						*
	F: CPT sodium citrate (blue/black)	PBMCs (adaptive immunity)				*^Δ^			*	*	*	
Urine	Maternal: urine pot Infant: collection bag	Metabolome/lipidome	*	*	*		*	*	*	*	*	
		Advanced glycation end products	*	*	*		*		*		*	
Stool	Maternal: EasySampler Infant: stool collection kit	Microbiome	*	*	*		*	*	*	*	*	
		Virology	*	*	*		*	*	*	*	*	
		Metabolome/lipidome	*	*	*		*	*	*	*	*	
Saliva	Oragene kit	SNP typing						*				*
Tongue dorsum	ESwab swab	Microbiome	*	*	*		*	*	*	*	*	
Buccal mucosa	ESwab swab	Microbiome	*	*	*		*	*	*	*	*	
Throat	UTM	Virology	*	*	*		*	*	*	*	*	
Nasal	ESwab swab	Microbiome	*	*	*		*	*	*	*	*	
Skin (inner elbows)	ESwab swab	Microbiome			*	* m&i	* m&i	* m&i	* m&i	*	*	
Vagina	ESwab swab	Microbiome			*							
Colostrum (day 0–3)	Colostrum collection kit	Microbiome				*						
		Metabolome/lipidome				*						
Breast milk	Milk collection kit	Microbiome					*	*ζ	*ζ	*ζ	*ζ	
		Metabolome/lipidome					*	*ζ	*ζ	*V3 ζ		
Diet	Maternal diet evaluation tools	DQES version 2			*			*ζ				
	Infant diet evaluation tools	Infant diary (birth-6 m)						*	*			
		Infant diary (6-12 m)								* V3	* V4	
		24 hour recall (12 – 24 months)								* V5, V7	* V6	
		Australian Toddler Eating Survey (>24 months)								* V9	* V8, V10	

**†** if available.

ψ or at first opportunity.

**††** if mother has T1D.

ϕ if persistent islet autoantibodies are detected.

^Δ^ cord blood.

^Ω^ using Guthrie Card if cord blood sample not taken.

“m&i” maternal and infant.

ζ if breast feeding.

### Estimation of target population

The population in the five states (New South Wales (NSW), Western Australia (WA), Queensland (Qld), Victoria (Vic) and South Australia (SA)) participating in ENDIA is 20.8 million, i.e. ~92% of Australia’s total population, and of these 3,500,000 men and 3,500,000 women aged 15–40 years [100]. Conservatively, there are 90,000 people with T1D in Australia, of whom ~15,000 are aged 0–14 years and ~45,000 aged 15–40 years, affecting men and women equally. Therefore, the prevalence of T1D among Australian women aged 15–40 years is 22,500/3,500,000 or 0.6%. Every year 250,000 women give birth in Australia, of whom 0.6% (n = 1,500) have T1D. There will also be 1,500 new fathers each year with T1D. Thus, approximately 3,000 births annually are to a parent with T1D. In contrast, the prevalence of siblings with T1D is relatively low. The incidence of T1D in children aged 0–14 is 22 per 100,000 person years [3]. Of 250,000 newborns each year in Australia, approximately half (125,000) will have a sibling. If the majority of those have a sibling aged 0–14 years, only ~28 will have T1D. Therefore, there are approximately 3,000 potential participants per annum of whom we aim to recruit 400–475 per year.

### Determination of sample size

We estimate recruitment of 1,400 participants from the five states over three years, followed for a median of two years with a 9% rate of persistent islet autoimmunity. Maximum total dropout /lost to follow-up rate is estimated at 15% with the majority of dropouts occurring in the first six months of follow-up. These estimates are based on data from the Australian BabyDiab [12] and TRIGR [93] at-risk birth cohorts in which dropout rates were 15% and 7%, respectively.

Using nQuery Advisor, with 600 participants above the median and 600 below (1200 total after 15% drop out from 1,400), for a given exposure variable, power is 90% to detect a difference between survival (i.e. no islet autoimmunity) of 93% in one group and survival of 88% in the other – with 108 events (islet autoimmunity) or 9% of the total sample of 1,200 required [101]. For examining interactions between uncorrelated exposure variables with approximately 375 participants per combination of above/below the median, the power is 77% to detect a difference in survival (no islet autoimmunity) between 93% and 87% (70 events in 600 participants required).

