**Methods/design:**

ENDIA is the only prospective pregnancy/birth cohort study in the Southern Hemisphere investigating the determinants of type 1 diabetes in at-risk children. The study will recruit 1,400 unborn infants or infants less than six months of age with a first-degree relative (i.e. mother, father or sibling) with type 1 diabetes, across five Australian states. Pregnant mothers/infants will be followed prospectively from early pregnancy through childhood to investigate relationships between genotype, the development of islet autoimmunity (and subsequently type 1 diabetes), and prenatal and postnatal environmental factors. ENDIA will evaluate the microbiome, nutrition, bodyweight/composition, metabolome-lipidome, insulin resistance, innate and adaptive immune function and viral infections. A systems biology approach will be used to integrate these data. Investigation will be by 3-monthly assessments of the mother during pregnancy, then 3-monthly assessments of the child until 24 months of age and 6-monthly thereafter. The primary outcome measure is persistent islet autoimmunity, defined as the presence of autoantibodies to one or more islet autoantigens on consecutive tests.

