### Recruitment, retention and withdrawal of participants

#### Inclusion criteria

The inclusion criteria for ENDIA are an unborn child with an FDR with T1D, targeting the mother for recruitment in first, second or third trimester of pregnancy, or an infant less than six months of age with a FDR with T1D.

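### The 90% power on 1,200 children does not apply to exposures measured from pregnancy samples, because the 1,400 include infants enrolled after birth

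*Protocol article*

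**What the plan says.** **Who is recruited.** The Summary of design says "Recruitment and consent will occur during pregnancy". The abstract defines the cohort differently: "The study will recruit 1,400 unborn infants or infants less than six months of age with a first-degree relative". The Inclusion criteria also admit postnatal entry ("or an infant less than six months of age with a FDR with T1D"), the Exclusion criteria provide for consent in postnatal recruitment, and the Recruitment section repeats the six-month limit. That section names pregnant women as the main focus but gives no planned share, cap or minimum.

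**What the power rests on.** Under Determination of sample size: "We estimate recruitment of 1,400 participants from the five states over three years", and "Maximum total dropout /lost to follow-up rate is estimated at 15" per cent. The calculation is then made "with 600 participants above the median and 600 below (1200 total after 15% drop out from 1,400), for a given exposure variable", with the result "power is 90% to detect a difference between survival (i.e. no islet autoimmunity) of 93% in one group and survival of 88% in the other" and 108 events required. Alpha and sidedness are not given. The statement is not limited to any class of exposure.

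**What needs pregnancy data.** Hypothesis 1 begins "The maternal microbiome during pregnancy and lactation differs in composition, diversity and functional products between mothers". Hypotheses 3 and 4 include weight gain and viral infection during pregnancy. Table 1 and the pregnancy-visit sections schedule maternal blood, stool, swabs, virology and weight by trimester, with cord blood and colostrum around birth. A footnote to Table 1 makes the first-trimester column conditional on availability.

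**The concern.** An infant who joins at, say, four months of age has no stored maternal sample from any trimester, and none can be collected later. Such a child counts towards the 1,200 but adds nothing to an analysis of the pregnancy microbiome, pregnancy metabolome or prospective pregnancy virology. The sample-size section nevertheless gives those exposures the full cohort.

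The abstract presents profiling from early pregnancy as the study's strength, so the affected exposures are central to it. Two things follow. A null result for a pregnancy exposure could be read as coming from a test with 90% power when the power was lower. And if the antenatal share falls during recruitment, nothing in the stated figures would show it.

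**Working it through.** **Inputs.** From Determination of sample size: 1,400 recruited, 15% dropout, 600 + 600 analysed, autoimmunity-free survival 93% vs 88%, 108 events, power 90%. Not stated and therefore assumed: alpha (5%, tried one- and two-sided) and f, the share of the analysed children with pregnancy samples (50% to 100%).

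**1. Is there a reserve?** 1,400 × 0.85 = 1,190, which the protocol rounds to 1,200. Dropout is the only deduction, so nothing is set aside for children without pregnancy samples.

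**2. Reproduce the stated 90%.** Event proportions are p1 = 0.07 and p2 = 0.12, with mean 0.095 and n = 600 per group.

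- Null standard error: √(0.095 × 0.905 × 2/600) = 0.01693.
- Alternative standard error: √((0.07 × 0.93 + 0.12 × 0.88)/600) = 0.01687.
- Power = Φ((0.05 − z × 0.01693)/0.01687).
- One-sided 5% (z = 1.645): Φ(1.313) = 90.5%.
- Two-sided 5% (z = 1.960): Φ(0.997) = 84.1%.

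The time-to-event form agrees. The hazard ratio is ln 0.88 / ln 0.93 = 1.76, with log 0.566. Schoenfeld power with 108 events is Φ(√108 × 0.566/2 − z), which is 90.3% one-sided and 83.7% two-sided. The stated figure is therefore reproduced at one-sided 5%.

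**3. Restrict to children with pregnancy samples.** Same effect, same median split, n = 600 × f per group, two-proportion formula. For example, at f = 0.8 (n = 480) the standard errors are 0.01893 and 0.01886, and one-sided power is Φ((0.05 − 1.645 × 0.01893)/0.01886) = Φ(1.00) = 84.1%.

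| Assumed antenatal share f | Children | Events (108 × f) | Power, one-sided 5% | Power, two-sided 5% |
|---|---|---|---|---|
| 100% | 1,200 | 108 | 90.5% | 84.1% |
| 90% | 1,080 | 97 | 87.7% | 80.1% |
| 80% | 960 | 86 | 84.1% | 75.3% |
| 70% | 840 | 76 | 79.7% | 69.6% |
| 50% | 600 | 54 | 67.2% | 55.1% |

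**4. Loss due to postnatal entry alone.** Each column must be compared with its own first row. At 10% postnatal the loss is 2.8 points one-sided (90.5 − 87.7) and 4.0 two-sided (84.1 − 80.1). At 20% it is 6.4 and 8.8 points, at 30% 10.8 and 14.5, and at 50% 23.3 and 29.0.

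**5. Recruits needed to keep 1,200 with pregnancy samples.** 1,200/(0.85 × f) gives about 1,569 at f = 90%, 1,765 at 80%, 2,017 at 70% and 2,824 at 50%.

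**The case against.** **The share may be small.** Recruitment is aimed mainly at pregnant women, and the listed sources are largely antenatal clinics, prospective parents and pregnant mothers. If only one child in ten joins after birth, the loss is 3 to 4 points. This stands as a limit on the size. It does not make the figure correct for pregnancy exposures, because no share or cap is given. The 50% row only marks the end of the assumed range; nothing in the document suggests it is expected.

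**A drop from 90% to about 80% at one-tenth postnatal.** A reader might infer this by setting the two-sided 80.1% against the stated 90%. That is not a like-for-like comparison: at two-sided 5% the full cohort already has only about 84%. Nor can the 90% be called wrong, since it reproduces at one-sided 5% and the article does not name alpha.

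**No pregnancy data at all.** This stronger reading is not supported. Table 1 lets demographics, pregnancy complications and delivery details be documented at a later opportunity. Total pregnancy weight gain is listed as a record and might come from notes, and the lactation part of hypothesis 1 remains measurable. What is lost is the prospective trimester samples and, for most such children, cord blood and colostrum.

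**The microbiome has its own analysis.** The analysis section assigns longitudinal microbiome changes to matched nested case-control comparisons, so the median-split calculation may not be the intended test for hypothesis 1. That is fair, but the cases for a pregnancy-sample comparison would still come only from antenatal recruits (108 × f). Antenatal viral infection is explicitly placed in the survival models.

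**Late entry.** A reader might also infer bias because postnatal recruits join after time zero while the models mention only right censoring. Cord blood apart, infant antibody tests start at 3 and 6 months and an event needs consecutive positive tests, so almost no event can precede entry. Handling of entry times may also be left to the SAP.

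**The article is condensed.** Separate power by exposure class could sit in the full protocol. The contradiction about recruitment and the unrestricted power claim are, however, on the page.

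**Conclusion.** The point holds in a limited form. The article contradicts itself on whether recruitment is confined to pregnancy. Its single power statement covers any exposure on a cohort that includes children who cannot have trimester samples. For exposures measured from those samples, the analysed number is below 1,200 and the power below the stated value whenever any child is enrolled after birth. First-trimester exposures fall further below, because women enrolled later in pregnancy also lack those samples.

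The size cannot be fixed from the document. Relative to the full cohort at the same alpha, the loss is about 3 to 4 points if 10% are postnatal and about 6 to 9 points if 20% are. These figures assume the protocol's effect size, a median split, and the same dropout and autoimmunity rates in antenatal and postnatal recruits. The direction does not depend on alpha. The stated power is not challenged for exposures that can be measured in every child.

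**What to change.** - Reconcile the Summary of design with the abstract and the Inclusion, Exclusion and Recruitment sections, so that one statement says who makes up the 1,400.
- In Determination of sample size, limit the 1,200 children and 90% power to exposures measured in all children.
- Add a separate, lower size and power for exposures that need pregnancy samples, based on an explicit planned antenatal share, and name alpha and sidedness for both statements. Note that first-trimester exposures have fewer children still.
- Track the antenatal share against its planned value during recruitment, since missed trimester samples cannot be recovered.

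The cost is rewording, one recruitment figure to follow, and a less favourable stated power for pregnancy exposures. No change to eligibility or visits is needed.

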Prospective studies, including our own, reveal the development of islet autoimmunity may occur at any point during the first years of life [12] through to adolescence [13], although recent data pooled from three large international cohorts have indicated the median age at seroconversion is 2.1 years [14]. Once persistent islet autoimmunity has developed the risk of progressing to T1D by 15 years of age is 12.7% in children with a single islet autoantibody, 61.6% in children with two islet autoantibodies and 79.1% in children with three islet autoantibodies compared with a 0.4% risk in children with no islet autoantibodies [14]. Moreover, progression to T1D is faster in children who: (a) seroconvert prior to three years of age, (b) have human leukocyte antigen (HLA) genotype DR3/DR4-DQ8, and (c) are female [14].

The aim of the Environmental Determinants of Islet Autoimmunity (ENDIA) study is to identify environmental factors, and gene-environment interactions, that contribute to and protect against the development of islet autoimmunity and progression to T1D in children genetically at-risk of T1D. We will follow 1,400 infants with a first-degree relative (FDR) with T1D prospectively from early pregnancy into childhood to investigate relationships between prenatal and postnatal environmental factors, and the development of islet autoimmunity and subsequent T1D. ENDIA will evaluate the microbiome, nutrition, bodyweight/composition, metabolome-lipidome, insulin resistance, innate and adaptive immune function and viral infections. A systems biology approach will integrate multi-omics analyses to explore hypotheses and mechanisms underlying the development of islet autoimmunity.

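### The stated 90% main-effect power is reached only with an undisclosed one-sided 5% test; at two-sided 5%, which the study's questions call for, it is about 84%

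*Protocol article*

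**What the plan says.** All of this is in the protocol article. Under Determination of sample size, a generic exposure is split at its median into two groups of 600, a total of 1,200 once dropout is allowed for. For that comparison the text says "power is 90% to detect a difference between survival (i.e. no islet autoimmunity) of 93% in one group and survival of 88" (per cent, for the second group). The event count attached to this claim reads: "with 108 events (islet autoimmunity) or 9% of the total sample of 1,200 required". No alpha and no sidedness accompany the figure.

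The next sentence gives 77% power for an interaction, for survival of 93% against 87%. It cites about 375 participants per combination of exposure levels, and then 70 events in 600 participants.

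The Background sets the aim as to "identify environmental factors, and gene-environment interactions, that contribute to and protect against the development of islet autoimmunity". Under Hypotheses, numbers 1 and 2 posit a difference in the microbiome and number 4 posits that viral infection alters risk, all without direction. Number 3, on accelerated weight gain and insulin resistance, posits an increase in risk.

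**The concern.** Group sizes, survival proportions, events and power are all stated, so the test size is the only free input and can be inferred. The inputs point to a one-sided 5% test. A study looking for both risk and protective factors would ordinarily test two-sided, and a reader who sees 90% power with no qualification will assume two-sided 5%.

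At stake is the type II error quoted for the planned effect, and the number of events the investigators believe they need before a null result for an exposure is informative.

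**Working it through.** **Inputs** (Determination of sample size): 600 per group; survival 0.93 and 0.88; 108 events; power 90%. Alpha is not stated. I assume 5% and try it one-sided (z = 1.645) and two-sided (z = 1.960).

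**Effect size.** Under proportional hazards, HR = ln 0.93 / ln 0.88 = 0.568, so |ln HR| = 0.566 and (1 − HR)/(1 + HR) = 0.2758.

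**Events implied by the stated survivals.** 600 × (0.07 + 0.12) = 114, which is 114/1,200 = 9.5%. The stated 108 is 9% of 1,200.

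**Formulas** (d events, equal groups, z for the test size):
- Schoenfeld: power = Φ(½√d · |ln HR| − z)
- Freedman: power = Φ(√d · (1 − HR)/(1 + HR) − z)
- Two proportions, pooled variance under the null: 7% vs 12%, 600 per group

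**Reproducing the stated figure: one-sided 5%.**
- Schoenfeld, d = 108: ½ × 10.392 × 0.566 = 2.942; 2.942 − 1.645 = 1.297; power 90.3%
- Freedman, d = 108: 10.392 × 0.2758 = 2.866; 2.866 − 1.645 = 1.221; power 88.9%

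Both sit at about 90%, so the stated power and event count are recovered.

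**The same inputs at two-sided 5%.**
- Schoenfeld, d = 108: 2.942 − 1.960 = 0.982; power 83.7%
- Freedman, d = 108: 2.866 − 1.960 = 0.906; power 81.7%

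| Method | One-sided 5% | Two-sided 5% |
|---|---|---|
| Schoenfeld, 108 events | 90.3% | 83.7% |
| Freedman, 108 events | 88.9% | 81.7% |
| Schoenfeld, 114 events | 91.6% | 85.6% |
| Freedman, 114 events | 90.3% | 83.8% |
| Two proportions | 90.5% | 84.1% |
| Simulated log-rank, 600 per group, 10,000 runs | 90.8% | 84.5% |

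A smaller Cox simulation (1,500 runs) gave 89.1% and 82.8%. No method reaches 90% at two-sided 5%.

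**Events for 90% power.** Schoenfeld: 4(z + 1.282)²/(ln HR)². Freedman: (z + 1.282)² × [(1 + HR)/(1 − HR)]².
- One-sided 5%: 106.9 and 112.6, rounded up 107 and 113, which bracket the stated 108
- Two-sided 5%: 131.1 and 138.2, rounded up 132 and 139, i.e. 11.0% to 11.6% of 1,200

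By two proportions at two-sided 5%, 721 per group would be needed instead of 600.

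**The interaction sentence.** For 93% vs 87%, HR = ln 0.93 / ln 0.87 = 0.521. Its three sizes imply different event counts: 375 per group gives 375 × (0.07 + 0.13) = 75, and 600 participants as 300 per group gives 300 × 0.20 = 60. Neither is the stated 70.

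| Reading | One-sided 5% | Two-sided 5% |
|---|---|---|
| 375 per group (75 events) | 86.0–88.1% | 77.8–80.6% |
| 70 events | 83.9–86.0% | 75.0–77.8% |
| 300 per group (60 events) | 78.6–81.0% | 68.4–71.4% |

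(Ranges span Freedman, two proportions where a group size is given, and Schoenfeld.) The stated 77% fits two-sided 5% on the first two readings and lies nearer one-sided 5% on the third.

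**The case against.** The strongest reply is that nothing stated is contradicted. No alpha is given, the 90% is arithmetically right for a one-sided 5% test, and a condensed article may leave the alpha to the full protocol. That stands as far as it goes: the figure is overstated only against two-sided 5%, and the omission alone would not be a finding. But the power figure itself is printed here, and it depends on a convention that does not match the aim or most of the hypotheses. A two-sided alpha in another document would make the 90% wrong; a one-sided alpha would not suit the questions.

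It can also be said that hypothesis 3 is directional. It is, and for that hypothesis alone a one-sided test could be argued. The power sentence, however, is written for any exposure and names no direction.

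Finally, this is an observational cohort with many exposures, analysed by survival models with time-dependent covariates. The median split is a planning illustration and not one confirmatory test, about 84% is still conventional power, and follow-up continues. All of that stands and limits the severity.

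**Conclusion.** The concern holds as a should-fix correction of a planning figure. For 93% vs 88% with 600 per group, two-sided 5% power is 82–84% at 108 events and 84–86% at the 114 events implied by the stated survivals. The type II error is therefore about 16% (14–18% across these methods) rather than 10%, and 90% would need about 132–139 events. This assumes proportional hazards, equal groups and a 5% level. The difference between 108 and 114 events is small and does not drive the conclusion.

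Stronger readings that the document does not support:
- A reader might infer that the 90% and 77% figures demonstrably use different test sizes. The interaction sentence mixes 375 per combination, 600 participants and 70 events, and which test size fits depends on which of these is used. The inconsistency of the denominators is established; a change of alpha is not.
- A reader might infer from the Background statement that "the median age at seroconversion is 2.1 years" that 9% cannot be reached at a median follow-up of two years. That figure is the median age among children who seroconverted in pooled international cohorts. It gives no cumulative incidence for this cohort, so it neither refutes the 9% nor supports a lower power estimate.
- 1,400 less 15% is 1,190; writing 1,200 is rounding.

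**What to change.** In Determination of sample size:
- State a two-sided alpha of 0.05.
- Restate the main-effect power as about 84% for 93% vs 88% with 600 per group, and the expected events as about 114 (9.5%).
- Note that 90% power would need about 132–139 events, which could accrue with longer follow-up. The article fixes no analysis date, so tying the analysis to an event count is an option and not a requirement.
- For the interaction figure, state the alpha, choose one denominator, and recompute the events and power from it.

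The cost is wording and one recalculation. No added recruitment is needed; keeping 90% would mean at most a later analysis.
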